## Methods/design

The design and report of this clinical trial protocol follows the Standard Protocol Items: Recommendations for Interventional Trials (SPIRIT) statement (Additional file 1). The study received approval from the Research Institutional Ethical Committee in Universidad El Bosque (PCI 2019-10718).

This is a 12-month multicentre single-group interventional study that aims at assessing in children the caries-control effectiveness of a pandemic-adapted CCI protocol (non-AGP and reduced in-office appointments’ time). The outcomes include primarily, tooth-level control of caries progression, and secondarily, child-level control of caries progression and caries risk; parents’ and dentists’ acceptability of care, and improvement in children’s oral health behaviours. Data will be collected in the 21 centres that agreed to participate, which are located in Argentina [2], Brazil [1], Colombia [7], Dominican Republic [1], France [1], Mexico [1], Perú [1], Portugal [1], Russia [1], The Netherlands [1], United Kingdom [1], United States [2], and Uruguay [1].

The study phases are based on the CCI 4D cycle (Fig. 1) and include: (1) a baseline examination (T0), corresponding to CCI steps 1D, 2D and 3D to be conducted by the examiner (E); (2) the basic management and intermediate care (CCI step 4D) to be conducted by the dental practitioner/s (DP); (3) two follow-up assessments during the 12-month care period: T1, at 5–5.5 months (3 months after end of basic management care) (E); T2, at 8.5 months, and (4) a final re-assessment at 12 months (T3) (E). The study flowchart is shown in Fig. 2.

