For 1D, remote combined with in-office assessment will be conducted with parents, including social/medical/behavioural risk factors (6 items); protective factors (3 items), and oral hygiene (3 items) and dietary (5 items) oral-health behaviours [3, 9, 10, 29, 31–34, 36]. Clinical risk factors (5 items) will be assessed in the dental clinic with the children, as 2D assessments. After assessing dental biofilm (Silness and Löe modified, [37]) , the other clinical assessments are conducted after toothbrushing, with the aid of a WHO probe and drying tooth surfaces and/or removing any dental biofilm only with cotton rolls/gauze (without using compressed air/water). Assessments at the tooth-surface level include: (1) caries lesions staging and activity assessment using the visual ICDAS-merged Epi criteria (Sound, Initial, Moderate microcavity/shadow, Extensive) active/inactive [35], and (2) presence and status of fillings (Optimal, Acceptable or Not acceptable) and sealants (Optimal or Not acceptable), modified from Cvar and Ryge [38], and at the tooth-level: (1) missing due to caries; (2) tooth close to exfoliation, and (3) dental sepsis as a clinical consequence of untreated caries, with the PuIpal Involvement-Roots-Sepsis Index (prs/PRS) modified from the PUFA Index [39] with/without toothache. Routine bite-wing radiographs are not included and only used in specific cases based on clinical need, not as part of the study protocol. For 3D, after synthesis of information from steps 1D and 2D the examiner conducts the personalised care plan, jointly with the child’s parent and the external DP. At the individual-level, a designed matrix based on CCI [9] weighs up the risk and protective factors against each other, classifying the patient’s caries risk into low or high, with a respective 9-month or 3-month risk recall interval. Another matrix, taking into account the COM-B behaviour model [29] weighs up the adequate vs. inadequate oral hygiene and dietary habits behaviours against each other, classifying the patient’s oral-health behaviour into adequate, inadequate or very inadequate. The individual-level risk management decisions will include homecare and clinical approaches/interventions, according to CCI and adapted for the pandemic (with non-AGP and including remote appointments when possible), including implementing a short behaviour-change tool. At the tooth-surface level, according to the synthesis of the clinical assessments defined in 2D, the type of care is defined per surface with non-AGP as: none, active monitoring (AM), non-operative care (NOC), tooth-preserving operative care (TPOC), and at the tooth-level as endodontics or extraction [9, 9].

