### Statistical analysis plan

All the baseline and follow-up the individual- and tooth-level data, the parents’ and dentists’ TEI data, and costs’ information will be digitally registered (after training) for each codified patient in each centre keeping data safely stored and with limited access, in a designed data base in Microsoft Excel (2010), that includes data quality assurance by validation of data. The data will be sent to the DMT at each time point. Data will be analysed by an independent statistician. All statistical tests will be two-tailed tests. The level of statistical significance for all two-sided tests will be set at 0.05. Parametric methods will be considered first. Data that do not meet or cannot be transformed to meet parametric assumptions will be analysed by non-parametric methods. Demographic and clinical features of the participants (centre, gender, age, caries risk, pain, filling status, prs/PRS); oral health behaviour, dental care acceptability and costs, as well as caries experience (DMFS and dmfs with the D component using ICDAS-merged Epi) [35] will be described using mean and standard deviation (SD) for quantitative variables and percentages for qualitative variables.

Regarding costs, the providers’ payment model of the centre will be described (Fee-for-service, Capitation, Salary-based and Pay-for-performance) [43]. For the description of costs, these will be converted to the United States Dollar (USD) under the average Market Representative Exchange Rate for the year 2021 (MRER-average).

ANOVA and Kruskal Wallis analyses will be used to compare the baseline characteristics between centres.

The caries risk control (subjects where risk was reduced from high risk or maintained in low risk), and the number of subjects with avoidance of extraction, pain, and failure of restorations/sealants, will be compared between baseline (T0) and 12-month follow-up (T3) examinations using χ^2^.

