For the analyses at the tooth-surface level, we will exclude teeth that needed a treatment involving AGP (endodontic treatment, surgical extraction, etc.). Caries progression has been defined for this study in terms of a change from the decided and delivered tooth-surface level care (T0, after the 4D basic management) to the tooth-surface level status at the 12-month follow-up (T3) (Fig. 2), as follows: (1) from a sound surface to a caries lesion, a sealant, a filling, or a missing tooth; (2) from a sealant to a caries lesion, a filling, or a missing tooth; (3) to a more severe caries score and/or an active status (or remaining active), and (4) from a filling to a caries lesion or a missing tooth. The severity/activity caries progression will be firstly assessed through descriptive analyses (number of subjects/surfaces) and a comparison in the number of active lesions at 1 year versus baseline will be applied (Wilcoxon test or paired *t* test based on results of the Shapiro Wilk normality test). Multilevel logistic regression will also be used for the surface level data analyses, exploring the clustering of surfaces within individuals, to estimate the association among characteristics variables and the outcomes.

Parents’ treatment evaluation inventory: Comparisons of parents’ treatment acceptability will be conducted between participants classified in baseline as low vs. high risk using Independent *t* test.

Dentists’ treatment evaluation inventory: The dentists’ treatment acceptability will be described.

Oral-health related behaviour classification will be compared between assessments (T0, T1, T2, T3) and between high and low-risk patients using *t* test.

The level of significance considered for all tests will be 5%.

Analyses to handle protocol non-adherence and missing data: Data of patients who leave before the end of the study will be handled separately. A *t* test analysis will be conducted to compare the baseline mean number of surfaces with caries experience (ICDAS-merged Epi dmfs/DMFS) [35] of those children who left the study during the 1-year follow-up period with that of those who remained in the study. If they’ve left after T1 and or T2, their parents TEI will be also compared with that of those who remained, as well as the children’s oral-health behaviour classification, and the caries progression.

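### Chi-square for T0 versus T3 in the same children, partly on transition outcomes that have no T0 value, and an unqualified t test on a three-level behaviour class over four visits, do not fit these secondary outcomes

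*Protocol article*

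**What the plan says.** The Methods/design section sets the frame: "This is a 12-month multicentre single-group interventional study". The same children are therefore examined at T0, T1, T2 and T3.

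The Statistical analysis plan section names two analyses that matter here.

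- **Risk and events.** The first outcome is defined as "The caries risk control (subjects where risk was reduced from high risk or maintained in low risk". It is joined by "the number of subjects with avoidance of extraction, pain, and failure of restorations/sealants". Together they "will be compared between baseline (T0) and 12-month follow-up (T3) examinations using χ^2". No paired variant is named.
- **Behaviour.** "Oral-health related behaviour classification will be compared between assessments (T0, T1, T2, T3) and between high and low-risk patients using *t* test". The section on baseline and follow-up oral examinations describes the variable as "classifying the patient’s oral-health behaviour into adequate, inadequate or very inadequate", that is, three ordered classes. The listed secondary outcome for behaviour is the proportion of children who improve.

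Elsewhere in the same section the article does say which form it means: a paired t test or Wilcoxon test for the number of active lesions, and an independent t test for parents' acceptability by risk group.

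**The concern.** A Pearson chi-square comparing two time points assumes two independent samples. Here each child appears in both, and a child's risk class at T3 is likely to resemble the class at T0. A variable defined by the move from T0 to T3 also cannot be compared with itself at T0. The named test therefore cannot be carried out on risk control as defined, and whoever runs it must choose a substitute comparison that the text does not describe.

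For behaviour, a t test handles two means at a time, while the plan has four visits and three classes. It also yields a difference in mean score, whereas the outcome listed is a proportion.

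There is no control arm, so change within the child is the main evidence on risk and behaviour. If the p-values for that change are wrong, a real improvement may be reported as not significant.

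**Working it through.** **Sample size used for the illustrations.** The article gives SD 2.5, means 1.3 and 2.1, two-sided 5% and type II error 10%. Then n per arm = 2 × (1.960 + 1.282)² × 2.5² / 0.8² ≈ 205.2, rounded up to 206, which reproduces the article's figure. The documents give no prevalence of high risk and no within-child correlation, so both are assumed below.

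**Reading 1: chi-square on the two margins (high-risk status at T0 versus T3).**

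- For paired data with prevalence p and correlation φ, Var(p̂₀ − p̂₃) = 2p(1 − p)(1 − φ)/n. Pearson uses 2p(1 − p)/n.
- With no true change, the statistic behaves like (1 − φ) times a chi-square on 1 df. The true type I error is then P(|Z| > 1.96/√(1 − φ)).
- This gives about 1.9% at φ = 0.3, 0.56% at φ = 0.5 and 0.03% at φ = 0.7.

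Simulation with n = 206 and T0 prevalence 30% or 50% agrees closely:

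| φ | Pearson type I error | McNemar type I error | Power for a 10-point drop, Pearson | Power for a 10-point drop, McNemar |
|---|---|---|---|---|
| 0.3 | 1.9–2.2% | 4.9–5.0% | 55–68% | 69–76% |
| 0.5 | 0.55–0.73% | 4.9–5.0% | 56–71% | 84–90% |
| 0.7 | 0.05–0.07% | 5.4% | 58–76% | 98–99.5% |

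At the same prevalence and correlation, the loss of power is about 9 to 40 points.

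Worked example with 206 children: 100 high at both visits, 24 high to low, 8 low to high, 74 low at both.

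- Margins: 124/206 = 60.2% and 108/206 = 52.4%.
- Pearson: pooled p = 232/412 = 0.563; χ² = (16/206)² / (2 × 0.563 × 0.437 / 206) = 2.53, p = 0.11.
- McNemar: (24 − 8)²/(24 + 8) = 8.0, p = 0.005.
- Paired difference: 16/206 = 7.8 points; SE = √(32 − 16²/206)/206 = 0.0269; 95% CI 2.5 to 13.0 points.
- Within-child correlation in this table: (100 × 74 − 24 × 8)/√(124 × 82 × 108 × 98) = 0.69, so it lies near the top of the assumed range.

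**Reading 2: chi-square on the T0 by T3 cross-table.** Take 104 high at both visits, 20 changing each way and 62 low at both. There is no net change and McNemar is 0. The association chi-square is 206 × (104 × 62 − 20 × 20)²/(124 × 82)² = 72.9. It shows that T3 status is related to T0 status, and nothing about change.

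**Reading 3: every child counted as having avoided the event at T0.** With k failures by T3, χ² = k/(1 − k/(2n)). For k = 4 and n = 206 this is 4/(1 − 4/412) = 4.04, p = 0.044. Four failures (1.9%) would then be significant against a T0 value true by construction.

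**Behaviour.** Four visits give 4 × 3/2 = 6 pairs. Six independent tests at 5% would have a family-wise error of 1 − 0.95⁶ = 26%. In simulation (classes split 40/40/20, latent correlation 0.3 to 0.7), paired t tests hold about 5% each and about 20% over the six. Unpaired t tests have 0.2% to 2.6% per comparison. Either form assigns equally spaced scores to the classes, and neither gives the proportion improving.

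**The case against.** Several points on the other side stand and limit the concern.

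- **A reader might infer that nothing in this comparison exists at T0.** The article does not support that. Risk class, filling and sealant status, teeth missing due to caries and toothache are assessed in the clinical examination, and T0 and T3 both include the full assessment. Those statuses can be compared over time, with a paired method. Only risk control, and avoidance as worded, lack a T0 value.
- **A reader might infer that the plan will produce false positives for risk.** That rests on the cross-table reading. The text speaks of comparing examinations, and under the more natural two-sample reading the test is conservative. The cost is lost power.
- **A reader might infer that the behaviour t test ignores the ordering or is unpaired.** A t test on scores 1, 2, 3 uses the order and adds an assumption of equal spacing. The article does not label it paired or unpaired, and an independent test is right for high versus low risk at one visit. The general fallback to non-parametric methods partly answers the scale objection, but not pairing or four visits.
- **A reader might infer that all repeated data are mishandled.** Active-lesion counts have a paired test, and surface data have a multilevel model.

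Chi-square might also be shorthand for McNemar's test, and a separate analysis plan may say so. But the article states pairing where it applies it to active lesions and does not do so here, and McNemar's test cannot be run on risk control either.

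**Conclusion.** The concern holds in limited form. As written, the chi-square comparison cannot be applied to risk control, or to avoidance as worded. Applied to the underlying statuses as two samples, it has a true type I error of about 0.05% to 2% instead of 5%, with a corresponding loss of power. These sizes rest on assumed within-child correlations of 0.3 to 0.7 and T0 prevalences of 30% or 50%; with correlation near zero the problem disappears. The worked contrast (p = 0.11 versus 0.005) is towards the strong end of that range.

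The behaviour t test is under-specified, allows up to six pairwise tests at 5%, and does not estimate the listed outcome.

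This should be fixed. It falls short of a must-fix because only secondary outcomes are affected: the primary outcome, the sample size and the conduct of the study are untouched.

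**What to change.** - **Transitions.** Report risk control, and avoidance of extraction, pain and restoration or sealant failure, as 12-month proportions with 95% CIs.
- **Binary statuses measured at both visits** (high-risk status, pain, filling or sealant failure). Compare T0 with T3 by McNemar's test and give the paired difference in proportions with its 95% CI. For fillings and sealants, state the denominator, because care during the study adds new ones.
- **Behaviour.** Report the proportion improving from T0 to T3 with its 95% CI. Replace the t tests with one repeated-measures ordinal analysis across the four visits and by risk group. An ordinal GEE or an ordinal mixed model would serve; the choice between them is secondary.

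The data for all of this are already to be collected. The cost is a change of wording in the analysis plan before the data are analysed, and a little more analysis work.

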		*In teeth close to exfoliation:* High-viscosity Glass Ionomer ART sealant + 5% NaF (1 time)/30–38% SDF (1 time)	
		*In deep cavities or reversible pulpitis (without other pulp symptomatology):* One-Step Excavation + ART	

If SDF is available in the centre and the parents or the child don’t accept to have it applied on anterior teeth, select an alternate option

In case of dental emergency/endodontic treatment need take an x-ray register the detection in 2D and 3D, and treat/refer, excluding that tooth

*AM* active monitoring, *NOC* non-operative care, *TPOC* tooth-preserving operative care, *ART* atraumatic restorative treatment, *NaF* sodium fluoride, *SDF* silver diamine fluoride

**Table 2 Tab2:** Caries OUT pandemic-adapted CCI-4D interventions at the tooth-surface level with non-AGP for permanent dentition

	4D at the surface level: permanent dentition		
ICDAS-merged epi score	Caries OUT modified CCI—Care option		
Initial caries			
Inactive	AM		
Active	NOC	*Fossae and fissure:*	*Smooth surfaces:*
		*Option 1*: High-viscosity Glass Ionomer ART sealant + 5% NaF (every 3 m)	5% NaF (every 3 m)
		*Option 2:* 30–38% SDF (every 6 m)/5% NaF (every 3 m)	
Moderate caries microcavity/shadow			
Inactive	AM		
	NOC	*Fossae and fissure:*	*Smooth surfaces:*
		*Option 1:* High-viscosity Glass Ionomer ART sealant	*Option 1:* 5% NaF (1 time)
		*Option 2:* 30–38% SDF (1 time)/5% NaF (1 time)	*Option 2:* High-viscosity Glass Ionomer ART sealant
Active	NOC	*Option 1*: High-viscosity Glass Ionomer ART sealant + 5% NaF (every 3–6 m)	
		*Option 2:* 30–38% SDF (every 6 m) (only in molar teeth)/5% NaF (every 3 m)	
	TPOC	*If there is a more advanced Moderate lesion and in a High-risk patient*: ART	
When considered it necessary, have a bitewing radiograph taken to assess the depth of the radiolucency and correlate it with the likelihood of dentine infection (in the middle dentine third). Register radiographic score in 2D, and combine it with the clinical score and the individual caries risk to decide in 3D the specific tooth-surface care plan (NOC/TPOC)			
Extensive caries			
Inactive	AM		
	NOC	High-viscosity Glass Ionomer ART sealant/30–38% SDF (1 time)/5% NaF (1 time)	
Active	NOC	30–38% SDF (every 6 m)	
	TPOC	ART	
	*In deep cavities or reversible pulpitis (without other pulp symptomatology):* One-Step Excavation + careful ART		

In case of dental emergency/endodontic treatment need take an x-ray register the detection in 2D and 3D, and treat/refer, excluding that tooth

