*AM* active monitoring, *NOC* non-operative care, *TPOC* tooth-preserving operative care, *ART* atraumatic restorative treatment, *NaF* sodium fluoride, *SDF* silver diamine fluoride

Interventions at both individual-and tooth surface level, will be conducted during the 12-month study period. After the 1-year follow-up (T3), no further interventions will be conducted for the study, but can be conducted separately if the centre decides to.

The strategies to improve adherence to interventions will include phone and text messages of next appointment reminders for parents and children; a remote communication channel with parents to answer questions and to motivate both the parents and the children to follow the study recommendations; reassuring the parents that in the practice the global SARS COV-2 biosafety guidelines including the use of PPE are being strictly followed. These strategies will also be used to promote participant retention and complete follow-up.

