### Outcomes

#### Primary health outcome

Mean number of tooth surfaces with avoidance of caries progression (ICDAS-merged Epi severity and/or activity).

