#### Secondary health outcomes

Proportion of subjects with avoidance of caries progression (ICDAS-merged Epi severity and/or activity).Proportion of subjects with avoidance of caries risk level increase/no control, and avoidance of extraction, pain, failure of the filling/sealant.Proportion of parents and dentists with high dental care process acceptability (measured with TEI).Proportion of children improving oral-health related behaviours.Description of dental care costs.

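### The surface-level analysis excludes teeth needing endodontics or surgical extraction without a time limit, so caries failures after basic management can drop out of the progression figures

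*Protocol article*

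**What the plan says.** All of this is in the protocol article.

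- **Exclusion.** The Statistical analysis plan section says of the tooth-surface analyses: "we will exclude teeth that needed a treatment involving AGP (endodontic treatment, surgical extraction, etc".
- **The same exclusion in the care tables.** The footnote under Table 1, repeated under Table 2, reads: "In case of dental emergency/endodontic treatment need take an x-ray register the detection in 2D and 3D, and treat/refer, excluding that tooth". Neither place says at which visit the need must arise.
- **When need can arise.** The Interventions section says that care at both levels "will be conducted during the 12-month study period". The section on baseline and follow-up examinations has a care plan derived again at T1 and T2.
- **Progression window.** The change is measured from "T0, after the 4D basic management) to the tooth-surface level status at the 12-month follow-up (T3".
- **What counts as progression.** For a sound surface, change "from a sound surface to a caries lesion, a sealant, a filling, or a missing tooth"; for a filled one, change "from a filling to a caries lesion or a missing tooth". A sealed surface that ends as a missing tooth also counts. The clause for surfaces that already carry a lesion mentions only severity and activity.
- **Primary outcome.** "Mean number of tooth surfaces with avoidance of caries progression (ICDAS-merged Epi severity and/or activity".
- **Child level.** A secondary outcome covers "avoidance of extraction, pain, failure of the filling/sealant". Endodontic treatment is in no listed outcome.

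**The concern.** The exclusion covers two different kinds of tooth. A tooth already beyond non-aerosol care at T0 was never a candidate for the intervention, and leaving it out is reasonable. A tooth that was managed at T0 and then deteriorated from caries to pulp involvement or surgical extraction within the 12 months is a clear failure of caries control. Under the undated rule both leave the analysis, so whether the second kind is analysed depends on its outcome.

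The study has one group, so no comparison arm could share or offset the distortion. The Discussion says that positive results would help to change the standard of care, so the absolute level of control is what readers will take away.

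**Working it through.** **1. The rules side by side.** Take a tooth managed at T0 that deteriorates from caries at month 8.

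| Event after basic management | Exclusion rule | Progression definition | Child-level outcomes |
|---|---|---|---|
| Surgical extraction | Tooth excluded | Progression if the surface was sound, sealed or filled | Counted as extraction |
| Non-surgical extraction | Not named | Progression if the surface was sound, sealed or filled | Counted as extraction |
| Endodontic need | Tooth excluded | Not named | Counted only if it shows as pain or a failed filling or sealant |

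The direct contradiction is in the first row. The third row is a gap. A surface filled at basic management and filled again after endodontics meets no progression clause, so lifting the exclusion alone would not count it. A surface that carried a lesion and was then lost is likewise not named as progression.

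**2. Direction of the effect.** Let a child have N surfaces, p of them progressed. The excluded tooth has s surfaces, k of them progressed.

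- *Number progressed:* p if the tooth is kept, p − k if it is excluded. It falls by k.
- *Number not progressed (the literal primary outcome):* N − p if kept, and (N − s) − (p − k) = (N − p) − (s − k) if excluded. It is unchanged when k = s and lower when k < s. It never rises.
- *Proportion controlled:* 1 − p/N if kept, 1 − (p − k)/(N − s) if excluded. It rises whenever k/s > p/N. In the least favourable case, one progressed surface of five, k/s = 0.20. With the planning means for p, the condition is N > 1.3/0.20 = 6.5 or N > 2.1/0.20 = 10.5 surfaces. Three five-surface teeth (15) already meet it.

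The multilevel logistic model works on surfaces, so it loses the same events.

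**3. The plan's own figure.** The sample size section gives means of 1.3 and 2.1 progressed surfaces, SD 2.5, type I error 0.05 and type II error 10%. Two-sided:

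n per arm = 2 × [2.5 × (1.960 + 1.282) / 0.8]² = 205.2, rounded up to 206.

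This reproduces the stated 206. The point does not depend on the sample size; the means serve only as a scale.

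**4. Size.** The documents give no number of such teeth. Assumption: 1 to 10 per 100 children, with either one surface or the whole tooth (4 to 5 surfaces) counted as progressed.

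Hidden surfaces per child = teeth per child × surfaces per tooth.

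- One surface: 0.01 × 1 = 0.01 to 0.10 × 1 = 0.10.
- Whole tooth: 0.01 × 4 = 0.04 to 0.10 × 5 = 0.50.

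The share of progression hidden is hidden / (observed + hidden), where the observed mean is the mean after exclusion.

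| Observed mean | One surface | Whole tooth |
|---|---|---|
| 1.3 | 0.01/1.31 = 0.8% to 0.10/1.40 = 7.1% | 0.04/1.34 = 3.0% to 0.50/1.80 = 27.8% |
| 2.1 | 0.01/2.11 = 0.5% to 0.10/2.20 = 4.5% | 0.04/2.14 = 1.9% to 0.50/2.60 = 19.2% |

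**The case against.** The strongest reply is that the rule was meant for T0 only. It speaks of teeth that needed such treatment, and the next sentence starts the progression window after basic management. The footnote ties exclusion to registration in 2D and 3D, which are done in full only at T0 and T3. On that reading, teeth beyond non-aerosol care are removed at planning and later losses count through the missing-tooth clauses. The reading is coherent and may be the intended one, but the text does not state it. With care running for 12 months and plans derived again at T1 and T2, the plain wording also covers later need. The article mentions a separate analysis plan that might settle the timing. That does not cure a rule the article itself states without a limit and sets against its own progression definition.

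Other objections stand and narrow the point:

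- A reader might infer that the primary outcome is inflated, or that the bias always favours the intervention. Read literally, that outcome counts surfaces without progression, and step 2 shows that exclusion cannot raise it and may lower it.
- A reader might infer that all extractions vanish. Only surgical extraction is named, and non-surgical extractions can still count as missing.
- Severe failures are not all hidden. The exclusion is confined to the surface-level analyses, extraction and pain are analysed per child, and pulpal involvement and sepsis are recorded at examination.
- A reader might set the effect against the planning difference of 0.8 surfaces. Matching it would take 0.8/5 = 0.16 to 0.8/4 = 0.20 fully failed teeth per child, or 16 to 20 per 100 children. Nothing in the documents supports such a rate. The 0.8 is also a between-arm difference carried over from the earlier randomised design, which this study does not test.

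**Conclusion.** The point holds in a limited form. As written, the exclusion selects on the outcome for teeth that fail from caries after basic management, and it contradicts the progression definition for surgical extraction. It lowers the number of progressed surfaces, raises the proportion of surfaces controlled and biases the surface-level logistic model. The literal count in the primary outcome is not inflated.

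The size is unknown. On the assumed 1 to 10 teeth per 100 children, 0.01 to 0.10 progressed surfaces per child are hidden with one surface per tooth, and 0.04 to 0.50 with whole teeth. The upper end needs both the highest assumed rate and all five surfaces counted. The contradiction with the missing-tooth clauses, and the direction for the number of progressed surfaces, do not depend on these assumptions.

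**What to change.** Change the analysis wording only; treatment and referral stay as they are.

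1. Limit the exclusion to teeth whose need for aerosol-generating treatment was recorded at T0, and say so in the analysis section and in both table footnotes.
2. Count endodontic need or caries-related extraction arising after T0 basic management as progression of the affected surfaces (all surfaces if extracted). Write this into the definition, including for surfaces that already carried a lesion or a filling.
3. Reconcile the exclusion with the missing-tooth clauses so that no tooth is both an event and an exclusion.
4. Report excluded teeth by time and reason.
5. Show the present rule as a sensitivity analysis.

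The footnotes already require the need to be registered in 2D and 3D, so no new examination is needed. The cost is a somewhat less favourable progression figure, by an amount that the count in item 4 will make visible.

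### The surface-level logistic model names clustering within children but not within teeth, so standard errors for factors constant across a tooth would be too small

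*Protocol article*

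**What the plan says.** The Statistical analysis plan section plans a multilevel logistic regression for the surface-level data, "exploring the clustering of surfaces within individuals". The purpose given is "to estimate the association among characteristics variables and the outcomes". The covariates are not listed there, and neither tooth nor centre appears as a level.

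The same section defines progression in four rules. Rule 1 runs "from a sound surface to a caries lesion, a sealant, a filling, or a missing tooth". Rules 2 and 4, for surfaces that start as sealed or filled, also include a missing tooth as an end state. Rule 3, for surfaces with a lesion, is "to a more severe caries score and/or an active status (or remaining active)" and does not list a missing tooth. Before any of this, "we will exclude teeth that needed a treatment involving AGP (endodontic treatment, surgical extraction, etc.)" applies to the surface-level analyses.

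The section on baseline and follow-up oral examinations separates surface-level from tooth-level records. Lesion stage and activity, fillings and sealants are scored per surface. Tooth loss is recorded "at the tooth-level: (1) missing due to caries", together with closeness to exfoliation and sepsis (prs/PRS). Care is mostly decided per surface, "and at the tooth-level as endodontics or extraction".

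**The concern.** The data have three natural levels: surfaces in teeth in children. The model as described has two. Once the child effect is accounted for, it treats the surfaces of one molar as no more alike than surfaces on opposite sides of the mouth. The trial's own outcome definition makes that untrue for a lost tooth, because one event produces several progressions.

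A factor that takes the same value on every surface of a tooth then appears to have more independent information behind it than it has. Its confidence interval is too narrow, and it is declared significant too often. Candidates are dentition (primary or permanent), tooth type (molar or anterior) and prs/PRS. Tables 1 and 2 vary care by the first two, and prs/PRS is among the clinical features listed for description in the analysis section.

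**Working it through.** **What the article gives.** It states no standard error, intraclass correlation or design effect for this model, so there is no figure of its own to reproduce on this point. Its one computed figure, the sample size, does reproduce: per arm, n = 2 × (1.960 + 1.282)² × 2.5² / 0.8² = 2 × 10.51 × 6.25 / 0.64 = 205.3, rounded up to 206. That number of children is used below.

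**Assumptions not in the article.** 20 teeth per child, 5 surfaces per tooth, intercept −3 and child standard deviation (SD) 1.0 on the logit scale, tooth SD from 0 to 2.0, and 0% to 3% of teeth lost and still in the analysis, with all five surfaces counted as progressed. Two factors with no true effect were entered. One is constant across a tooth (present on 40% of teeth at random). The other varies within the tooth (one surface against the other four).

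**Method.** The model as described (logistic, child random intercept only) was fitted by maximum likelihood with 15-point Gauss-Hermite quadrature, 300 replicates per setting. The Monte Carlo error of a rejection rate is √(0.05 × 0.95 / 300) = 1.3 points at 5% and √(0.20 × 0.80 / 300) = 2.3 points at 20%. The ratio shown is the mean model standard error divided by the true sampling SD of the estimate; 1.00 is correct.

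| Tooth SD | Teeth lost | Tooth-constant factor: ratio | Type I error | Within-tooth factor: ratio | Type I error |
|---|---|---|---|---|---|
| 0 | 0% | 1.01 | 4.3% | 0.99 | 3.7% |
| 1.0 | 0% | 0.79 | 13.7% | 1.02 | 4.7% |
| 1.5 | 0% | 0.73 | 15.3% | 1.16 | 1.7% |
| 2.0 | 0% | 0.67 | 19.3% | 1.24 | 1.0% |
| 0 | 1% | 0.87 | 9.3% | 1.06 | 4.3% |
| 0 | 3% | 0.68 | 18.7% | 1.31 | 1.3% |
| 1.0 | 2% | 0.68 | 20.0% | 1.09 | 3.3% |

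**Reading the table.**
- The top row shows that the method is calibrated when there is no tooth effect.
- For the tooth-constant factor, the shortfall in the standard error runs from 1 − 0.87 = 13% to 1 − 0.67 = 33%.
- The ratios and rejection rates agree with each other. With type I error = 2 × (1 − Φ(1.96 × ratio)), a ratio of 0.87 gives 2 × (1 − Φ(1.71)) ≈ 9%, and 0.67 gives 2 × (1 − Φ(1.31)) ≈ 19%.
- The two rows with tooth loss and tooth SD 0 show that the missing-tooth rule is enough to produce the problem, with no other correlation within teeth.
- For the within-tooth factor, no setting with tooth dependence gives a standard error that is too small.

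**Low end.** A separate simulation with the same numbers of children, teeth and surfaces and the same child SD gave a type I error of about 6% at tooth SD 0.7 with no loss, which cannot be told apart from 5% at this precision. At tooth SD 1.0 with no loss it gave a standard error 14% too small and type I error of about 10%, somewhat milder than the table.

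**Not checked.** The three-level model itself was not fitted.

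**The case against.** Several points on the other side stand.

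- **Role of the model.** It is an additional association analysis. The primary outcome is a mean number of surfaces, and the stated comparison of active lesions at one year with baseline is a Wilcoxon or paired *t* test. Neither uses this model's standard errors.
- **Covariates.** The article does not say that dentition or tooth type will be entered. Many of the features it lists (centre, gender, age, caries risk) belong to the child or the centre. The point applies only if tooth-constant factors are used.
- **Inputs.** Tooth variance and tooth loss are assumed. The simulated loss turns all five surfaces into progressions, whereas rule 3 does not list a missing tooth for surfaces with a lesion, and some lost teeth leave through the exclusion of teeth needing aerosol-generating treatment. The 1% to 3% must be read as teeth lost and kept in the analysis.
- **Level of detail.** An article may leave the full random-effects structure to a separate analysis plan, and the word exploring does not rule out further levels. This stands only in part: the article does name the clustering it has in mind, and that structure, followed as written, has the defect shown.

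A reader might also infer two stronger things that the documents do not support. One is that the rules make all surfaces of a tooth progress together. Only a missing tooth forces that; new lesions, sealants, fillings, severity and activity are judged surface by surface, and a Hall crown placed in basic management is part of the starting state, since progression is counted from after that care. The other is that standard errors for surface-level factors are too small as well. For factors that vary within a tooth, the simulation shows them about right or too large. Initial severity and type of care are mostly set per surface, so they share the problem only as far as they are common to a whole tooth.

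**Conclusion.** The point holds for factors that are constant across a tooth. If such factors are entered in the two-level model as described, their standard errors are about 13% to 33% too small, and type I error is about 9% to 20%, roughly two to four times nominal. This is under an assumed tooth SD of 1.0 to 2.0 on the logit scale, tooth loss of 1% to 3%, or both. The documents give neither quantity, and with little tooth variance and no retained tooth loss the effect is negligible. Findings on child-level factors and on the primary comparison are not put in doubt by this point. It is worth correcting because this is the only regression named for the surface-level data and all tests are judged at 5%.

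**What to change.** State the model as surface within tooth within child, by adding a tooth-level random intercept to the child-level one. Name the fallback in advance: if the model does not converge, fit a marginal logistic model with robust standard errors clustered by child. Clustering by child covers dependence within teeth, since every tooth belongs to one child. Clustering by centre would cover it too, but with only 21 centres robust standard errors tend to be too small, so it should not be relied on without a small-sample correction.

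The cost is a change of analysis wording, a slightly slower fit and possible convergence trouble, which the fallback handles. The marginal model estimates population-averaged odds ratios rather than odds ratios conditional on child and tooth, so the report should say which were used. No new data are needed, because tooth-level records are already collected.
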